### Equipment

Body mass and stature will be determined using a duly calibrated mechanical scale (Welmy brand) with a 150-Kg capacity and precision of 0.1 Kg and stadiometer coupled to the scale with a precision of 0.1 cm.

Static balance will be evaluated using a force plate (Kistler, model 9286BA), which allows stabilometric analysis based on oscillations of the center of pressure. The acquisition frequency will be 400 Hz, captured by four piezoelectric sensors positioned at the ends of the platform, measuring 400/600 mm. The data will be recorded and interpreted using the SWAY software program designed by BTS Engineering, integrated to and synchronized with the SMART-D 140® system.

The SMART-D 140® system (BTS Engineering) will be used for the three-dimensional evaluation of gait, using eight cameras with an infrared-sensitive response and the 32-analog channel SMART-D INTEGRATED WORKSTATION®. The kinetic data will be collected using two force plates (Kistler, model 9286BA) for recording displacement from the center of pressure and the contact time between the foot and surface of the platform. An eight-channel, wireless-transmission electromyograph (FREEEMG® – BTS (Engineering) will also be used, with bipolar electrodes with a total gain of 2000 x and within a frequency of 1000HzHz. The impedance and common rejection mode will be >10^15^ Ω//0.2 pF and 60/10Hz 92 dB.

The posture-control insoles to be used by the children in the experimental group have surface, middle and deep portions. The surface portion is composed of fabric that covers the other portions and serves to absorb sweat and provide comfort. The middle portion is made of ethylene vinyl acetate (EVA) with a thickness of 3 mm. The lowest portion is made by material formed by a network of cotton fibers and resin with a thickness of 1 mm in which the podal pieces are located (bars, wedges and shims), made from EVA with respective thicknesses, densities and resilience, the aim of which is to stimulate the skin in predetermined regions and promote postural reprogramming [14]. In the study proposed, the pieces to be used will be the hard postural half moon, wedge and outer anti-rotator, with the aim of acting on the re-equilibrium of a common motor pattern (Figure 1).

**Figure 1 F1:**
[figure not shown]
Representation of podal piece to be used in making of the posture-control insoles.

After the different portions and the foot piece to be used are positioned, thermal molding of the insole will be performed for the fusion of the different sections and pieces (Figure 2). All material used for the confection of the insoles are from the brand name Podaly®.

**Figure 2 F2:**
[figure not shown]
Representation of insoles after thermal molding; A – Front view; B- Side view, showing three portions.

### Instruments

The Gross Motor Function Classification System for Cerebral Palsy (GMFCS) will be used to classify the children based on the level of gross motor function [17]. This system classifies children between Levels I and V. Only children classified at Levels I and II will participate in the proposed study.

The motor growth curves [18] referring to GMFCS Levels I, II and III will be used as a complement to the classification of gross motor function. The curves have the scoring of the GMFM-66 [19,20] on the vertical axis and age on the horizontal axis for each GMFCS level. Using these curves, the child is functionally classified as being within the expected range, better than expected or poorer than expected.

The Berg Balance Scale will be used for the assessment of functional balance. This scale consists of 14 tasks that are similar to different activities of daily living. The items are scored on a five-point scale ranging from 0 (inability to perform task) to 4 (ability to perform task independently). The maximal score is 56 points. The point system is based on the time in which a position is maintained, the distance to which the upper limb is capable of reaching out in front of the body and the time needed to complete a task. The execution time is approximately 20 minutes. A chronometer, stool and chair are needed for the assessment. The evaluation is performed with the child dressed and making use of his/her habitual orthosis and/or gait assistance device [21,22].

The Timed Up-and-Go Test will be performed and distance will be measured using a metric tape. This fast, practical, easy-to-apply test is widely used for the assessment of functional mobility and dynamic balance. The test quantifies functional mobility through the time (in seconds) in which an individual performs the task (stand up from a standardized chair with back and arm supports, walk three meters, turn around, walk back to the chair and sit down again) [23,24].

The Six-Minute Walk Test will be performed. This test is a reliable measure for the assessment of physical fitness [25,26] and quantifies (in meters) functional mobility through the distance traveled walking in six minutes. This test will be performed based on the guidelines of the American Thoracic Society.

The modified Ashworth Scale will be used for the classification of hypertonia. This scale consists of Item 1+ and a five-point scoring system ranging from 0 (absence of tonic alteration) to 4. The classification of severity is related to range of motion at which increased resistance to rapid passive movement is detected [27].

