**Methods/Design:**

The sample will be composed of 24 children with CP between four and 12 years of age. After the signing of the statement of informed consent, the children will be randomly allocated to two groups: a control group using AFOs alone and an experimental group using both posture-control insoles and AFOs. Evaluations will be performed on five occasions: without any accessory (insoles or AFOs), immediately after, one month after, six months after and one year after AFOs or insole and AFOs use. The evaluation will involve the analysis of gait, static and functional balance, mobility and hypertonia. The three-dimensional assessment of gait will involve the eight-camera SMART-D SMART-D 140® system (BTS Engineering), two Kistler force plates (model 9286BA) and an eight-channel, wireless FREEEMG® electromyography (BTS Engineering). Static balance will be assessed using a Kistler force plate (model 9286BA). Clinical functional balance and mobility will be assessed using the Berg Balance Scale, Timed Up-and-Go Test and Six-Minute Walk Test. The posture-control insoles will be made of ethylene vinyl acetate, with thermal molding for fixation. The fixed orthoses will be made of polypropylene and attached to the ankle region (AFO). The results will be analyzed statistically, with the level significance set to 5% (p < 0.05).

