### Procedures

The children selected (whose legal guardians agreed to their participation by signing a statement of informed consent) will be evaluated regarding their anthropometric data and GMFCS classification and randomly allocated to the experimental and control groups. The control group will make daily and constant use of the AFOs. The experimental group will make use of the posture-control insoles for six hours daily during the most active period of the day and will remain using the AFOs the rest of the day.

The evaluation process (before, immediately after, one month after, six months after and one year after insole use) will be performed under two different conditions. Under the first condition (evaluation 1), the children will not use an assistance device and under the second condition (evaluation 2), the children will use either the posture-control insoles or the AFOs, depending on the group to which they belong. Evaluation 1 and evaluation 2 will be performed by different examiners. Examiner 1 will not be aware of which group the children belong, thereby characterizing the investigation as a blind study.

The evaluations will be held on two non-consecutive days. The Berg Balance Scale, Timed Up-and-Go Test, Six-Minute Walk Test and modified Ashworth scale will be administered on the first day. The three-dimensional gait analysis and the static balance test on a pressure plate will be performed on the second day.

For the three-dimensional gait analysis, the equipment will be introduced to the children and the procedures will be explained. The children will be submitted to an initial practice gait exam to become familiarized with the procedure (no data will be collected on this training run). The children will wear bathing suits to facilitate the placement of the markers. The skin will be cleaned with alcohol for better attachment of the markers on the exact sites. The markers will be enveloped in adhesive tape lined with microscopic glass spheres and attached to a plastic base with double-sided adhesive tape. The markers will be attached to the children in the orthostatic position, as suggested by Davis et al. (1991), [28] on the following anatomic structures:

Pelvis: Three markers will be positioned on the anterior superior iliac spines (right and left) and one between the posterior superior iliac spines.

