### Statistical analysis

The Kolmogorov-Smirnov test will be used to test the data with regard to Gaussian distribution. Central tendency and dispersion measures will be expressed as mean and standard deviation values or median and inter-quartile interval when exhibiting parametric and non-parametric distribution, respectively. Either repeated-measure ANOVA or Friedman’s test will be used for the intra-group analysis and either one-way ANOVA or the Kruskal-Wallis test will be used for the inter-group analysis for data with parametric and non-parametric distribution, respectively. The data will be organized and tabulated using the Statistical Package for the Social Sciences (SPSS v.19.0). The level of significance will be set to 5% (p < 0.05).

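### A normality test decides whether the modified Ashworth grade, an ordered classification, is averaged and tested by ANOVA; it should go to a rank or ordinal method in every case

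*Protocol article*

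**What the plan says.** Hypertonia is one of the evaluated domains in the abstract's Methods/Design: "The evaluation will involve the analysis of gait, static and functional balance, mobility and hypertonia". The Instruments section names the tool and its purpose: "The modified Ashworth Scale will be used for the classification of hypertonia". It then describes the scale: "This scale consists of Item 1+ and a five-point scoring system ranging from 0 (absence of tonic alteration) to 4". Under Procedures, the "modified Ashworth scale will be administered on the first day" of the evaluations.

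The Statistical analysis section has one rule for all data. First, "The Kolmogorov-Smirnov test will be used to test the data with regard to Gaussian distribution". The summary then follows from that result: "Central tendency and dispersion measures will be expressed as mean and standard deviation values or median and inter-quartile interval". So do the tests. Within groups: "Either repeated-measure ANOVA or Friedman’s test will be used for the intra-group analysis". Between groups: "either one-way ANOVA or the Kruskal-Wallis test will be used for the inter-group analysis". No outcome is exempt, and nothing separates ordered classifications from measurements.

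**The concern.** A non-significant normality test does not turn ordered grades into a measurement. The distances from 1 to 1+ and from 1+ to 2 are not defined by the scale, yet a mean or an ANOVA has to use them. As written, the rule can send the modified Ashworth grade to the mean and ANOVA branch, where someone must choose a number for 1+. At least two choices keep the grades in order: 1+ as 1.5, or the six grades renumbered 0 to 5. They give different means and can give different p-values from the same children.

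At stake is the between-group and within-group reading of one listed outcome. A small sample makes it worse, because a normality test on 12 values seldom rejects unless the departure is gross.

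**Working it through.** **Inputs from the protocol article.** Two groups of 12 (Sample description and characterization), significance level 5%, six ordered grades (Instruments), and the normality-gated choice between ANOVA and rank tests (Statistical analysis). The 12 per group was derived for cadence (17 steps/minute, SD 15). The two-sided normal formula gives 2 × [15 × (1.960 + 0.842) / 17]² = 12.2, so the stated 12 is reproduced to within rounding. No figure is given for the Ashworth outcome.

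**Assumptions.** The article gives no grade distributions, so those below are assumed. The normality test is applied to each arm separately.

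**Step 1: is the ANOVA branch reachable?** With 1+ kept as its own level, a single sample of 12 assumed grades passes the uncorrected Kolmogorov-Smirnov test about 98–99% of the time under one set of distributions. Across several assumed group differences, both arms passed in about 50–95% of trials. With the Lilliefors correction both arms passed in only about 0.2–20%. The article does not say which form applies.

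**Step 2: one dataset worked by hand.** It was picked from simulated trials because the two order-preserving codings disagree, so it shows that a flip is possible, not how often. Counts at 0/1/1+/2/3/4 are 0/3/3/2/4/0 and 3/3/3/2/1/0. Both arms pass both forms of the test under both codings. For two groups of 12, F = 6d² / (SS within / 22), where d is the difference in means.

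- 1+ = 1.5: means 23.5/12 = 1.958 and 14.5/12 = 1.208, d = 0.75. SS within = 7.729 + 9.229 = 16.958; /22 = 0.771. F = 3.375/0.771 = 4.38, p = 0.048.
- Grades renumbered 0–5: means 31/12 = 2.583 and 19/12 = 1.583, d = 1.00. SS within = 16.917 + 18.917 = 35.833; /22 = 1.629. F = 6/1.629 = 3.68, p = 0.068.
- Kruskal-Wallis: p = 0.076 under either coding, because the ranks are the same.

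**Step 3: how often, and at what cost?** Simulated rejection rates at 0.05, 12 per arm, 1+ kept distinct, ANOVA applied without the normality gate:

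| Assumed grades 0/1/1+/2/3/4, %, one arm v the other | ANOVA, 1+ = 1.5 | ANOVA, 0–5 | Kruskal-Wallis |
|---|---|---|---|
| 5/20/35/30/10/0 v 20/40/25/10/5/0 | 40% | 43% | 44% |
| 10/30/40/15/5/0 v 20/50/20/10/0/0 | 26% | 28% | 29% |
| 0/15/55/25/5/0 v 5/60/25/10/0/0 | 70% | 71% | 71% |
| 5/20/30/30/15/0 v 20/40/25/10/5/0 | 45.8% | 49.6% | 50.3% |
| 10/30/30/20/10/0 in both | 5.1% | 5.3% | 5.7% |

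ANOVA is therefore 0 to about 5 points below Kruskal-Wallis when groups differ, and error rates are near 5% when they do not. The two codings disagreed on p<0.05 in about 1–7% of trials across these settings. Kruskal-Wallis never disagreed between them (0%).

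**The case against.** The strongest reply has four parts.

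- **The rank branch is already in the plan.** This is true: when the normality test rejects, the analysis is already median, quartiles, Friedman and Kruskal-Wallis. With the Lilliefors form as the gate, the first three settings above reach ANOVA in 16%, 5% and 0.4% of trials, and the two codings then disagree in 1.2%, 0.3% and 0.1%. The safeguard works only if that form is used, and the article does not fix it.
- **A numeric code for 1+ is a detail for an analysis plan that is not shown.** This also stands. The absence of a code is not the point. The point is the stated rule that lets this scale be averaged at all.
- **The description of the scale might be read as a contradiction**, with a grade 1+ set against a five-point score. The text does not support that. It lists 1+ in addition to the five points, which is loosely worded but coherent as six ordered grades.
- **A reader might infer that a five-point score means 1+ is merged into 1.** Merging would be costly. In the third setting ANOVA power is 27% merged against 70% with 1+ = 1.5, and the three codings disagree in 45% of trials. But nothing in the article calls for merging, and naming 1+ as its own item points the other way. Merging would also cost Kruskal-Wallis power, so it is not an ANOVA problem. Those figures do not measure a defect of this plan.

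**Conclusion.** The point holds in a limited form. The Statistical analysis section lets a weak normality test decide whether an ordered six-grade classification is treated as a measurement, and on that branch the result depends on an arbitrary value for 1+. The harm is small: at most about 5 power points, about 1–7% of trials with a coding-dependent decision before any gating, and no inflation of type I error. It touches one outcome that is not named as primary and does not drive the sample size.

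These sizes rest on assumed grade distributions, on 12 children per arm, and on 1+ being kept distinct. Only the between-group comparison was simulated. The within-group case follows by reasoning: repeated-measures ANOVA also needs a number for 1+, whereas Friedman's test uses only ranks within each child.

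**What to change.** In the Statistical analysis section, exempt the modified Ashworth grade from the normality-gated rule. State that:

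- it has six ordered grades, 0 < 1 < 1+ < 2 < 3 < 4, with 1+ kept as its own grade;
- it is reported as the number of children at each grade, or as median and quartiles of the ordered grade;
- groups are always compared by a rank or ordinal method (Wilcoxon/Kruskal-Wallis, or a proportional-odds model), and within-group change is tested by Friedman's test, whatever the normality test shows.

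This costs a sentence or two of wording. It needs no new data, visits or children. The one small loss is that hypertonia is no longer reported as a mean.

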### Procedures

The children selected (whose legal guardians agreed to their participation by signing a statement of informed consent) will be evaluated regarding their anthropometric data and GMFCS classification and randomly allocated to the experimental and control groups. The control group will make daily and constant use of the AFOs. The experimental group will make use of the posture-control insoles for six hours daily during the most active period of the day and will remain using the AFOs the rest of the day.

The evaluation process (before, immediately after, one month after, six months after and one year after insole use) will be performed under two different conditions. Under the first condition (evaluation 1), the children will not use an assistance device and under the second condition (evaluation 2), the children will use either the posture-control insoles or the AFOs, depending on the group to which they belong. Evaluation 1 and evaluation 2 will be performed by different examiners. Examiner 1 will not be aware of which group the children belong, thereby characterizing the investigation as a blind study.

The evaluations will be held on two non-consecutive days. The Berg Balance Scale, Timed Up-and-Go Test, Six-Minute Walk Test and modified Ashworth scale will be administered on the first day. The three-dimensional gait analysis and the static balance test on a pressure plate will be performed on the second day.

For the three-dimensional gait analysis, the equipment will be introduced to the children and the procedures will be explained. The children will be submitted to an initial practice gait exam to become familiarized with the procedure (no data will be collected on this training run). The children will wear bathing suits to facilitate the placement of the markers. The skin will be cleaned with alcohol for better attachment of the markers on the exact sites. The markers will be enveloped in adhesive tape lined with microscopic glass spheres and attached to a plastic base with double-sided adhesive tape. The markers will be attached to the children in the orthostatic position, as suggested by Davis et al. (1991), [28] on the following anatomic structures:

Pelvis: Three markers will be positioned on the anterior superior iliac spines (right and left) and one between the posterior superior iliac spines.

Thigh: One marker will be placed laterally to the greater trochanter. A second marker will be placed laterally to the lateral condyle of the femur. A third marker will be positioned on an appendicular line midway between the two previous points.

Leg: One marker will be placed laterally to the head of the fibula. A second marker will be placed laterally to the lateral malleolus. A third marker will be positioned on an appendicular line midway between the two previous points.

Foot: A marker will be placed laterally to the head of the fifth metatarsus. One adjunctive marker will be placed bilaterally on heel only for the standing acquisition, before the walking test.

The markers will be used as reference for the eight-camera SMART-D BTS^@^ system which will acquire the 3D coordinates (x,y,z) of each marker [29]. The set of markers will be used to estimate the position of the joint centers and calculate the three-dimensional kinematics of the pelvis, hips, knees and ankles [30]. This will be performed through the combination of coordinates, which will take the information obtained from the positioning of the markers into consideration [29].

For such, the children will walk on a track marked on the ground measuring 90 centimeters in width and four meters in length, with two force plates (model 9286A) positioned in the center. Upon stepping on the force plates while walking, the kinetic gait data will be collected and calculated using a video system (BTS, Milan, Italy) synchronized to the two force plates.

The electrical activity stemming from the activation of the rectus femoris, tibialis anterior and soleus muscles (on right and left leg) will be collected using a signal conditioner (FREEEMG®, BTS). For the placement of the six channels, the motor point of the muscles will be identified and the area will be cleaned with 70% alcohol to reduce impedance, based on the recommendations of the Surface Electromyography for the Non-Invasive Assessment of Muscles.^(31)^ All electromyographic data will digitized in 1000 frames/second using the BTS MYOLAB® software program. The kinematic and kinetic data will be collected simultaneously and managed using the BTS® system and Smart Capture® software program.

Static balance will be analyzed using a Kistler force plate (model 9286BA). The evaluation will be performed with the individuals in the orthostatic position on the force plate with no restriction regarding the foot base. Readings will be taken three times under two conditions (eyes open and eyes closed), with each reading lasting 30 seconds. A rest period will be respected between each application of the instrument and the child will be allowed to interrupt the evaluation to rest at any time.

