### Sample description and characterization

The sample size will be calculated based on the study carried out by Buckon et al. (2004)[15] with results on gait cadence in children with CP (GMFCS Levels I and II) with and without a fixed AFO. For an expected size effect of 17 steps/minute, with a standard deviation of 15 steps/minute and assuming an α risk of 0.05 and an 80% power, the sample was estimated at 12 children per group. Thus, the sample will be composed of 24 male and female children with CP aged four to 12 years**.**

The participants will be recruited and selected for eligibility based on the criteria listed below.

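### The one-year within-arm tests cannot separate a device effect from growth, and the unadjusted between-arm test leaves the age spread of children aged 4 to 12 in the error term

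*Protocol article*

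**What the plan says.** All references are to the protocol article.

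- **Population** (Sample description and characterization): "the sample will be composed of 24 male and female children with CP aged four to 12 years".
- **Visits** (Procedures): "before, immediately after, one month after, six months after and one year after insole use". Both arms follow the same visits. At each visit the child is tested once without a device and once with the assigned device.
- **Size-dependent outcomes.** The sample size rests on raw cadence: "For an expected size effect of 17 steps/minute, with a standard deviation of 15 steps/minute". The Instruments section says the Six-Minute Walk Test "quantifies (in meters) functional mobility through the distance traveled walking in six minutes", and the Timed Up-and-Go is in seconds.
- **What is known at entry** (Procedures): children "will be evaluated regarding their anthropometric data and GMFCS classification and randomly allocated to the experimental and control groups". The Equipment section lists a scale and stadiometer and names no visit for them.
- **Age and motor function** (Instruments): the GMFM-66 growth curves have "age on the horizontal axis for each GMFCS level". They are used only to place a child relative to expectation.
- **Analysis** (Statistical analysis): repeated-measures ANOVA or Friedman's test within each group; one-way ANOVA or Kruskal-Wallis between groups. No baseline value, age or GMFCS level enters either test as named.

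**The concern.** Two separate problems follow from the named tests.

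First, the question of change over time goes to a test run inside each arm. Over a year a child's cadence, walking distance and test times shift with growth and maturation, whatever is worn. A significant time effect in one arm, or in one arm and not the other, could then be read as a device effect when growth alone would produce it. Growth could equally mask a real change.

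Second, the between-arm test ignores characteristics that are recorded before treatment and are likely to predict these outcomes. The age range is eight years and each arm has 12 children, so age-driven spread sits in the error term and the arms can differ in age by chance. The article itself recognises that motor function moves with age, but uses this only for classification.

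**Working it through.** **1. The plan's own figure.** Inputs from Sample description and characterization: difference 17, SD 15, alpha 0.05 (sidedness not stated), power 80%.

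n per arm = 2 × (1.960 + 0.842)² × (15/17)² = 2 × 7.849 × 0.7785 = 12.2

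This agrees with the stated 12 to within rounding. Power at 12 per arm is 0.793 by the normal approximation and 0.756 by the two-sided t test. The second is the reference below.

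**2. Does growth bias the between-arm comparison?** Simulation with no treatment effect. Assumptions: ages uniform on 4-12, age slope 3 units/year, other between-child SD 12, measurement-error SD 6, and common one-year growth of 0, 3, 5 or 8 units. The between-arm type I error stayed at 0.050-0.051. Growth common to both arms cancels.

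**3. Does growth enter the within-arm comparison?** Same assumptions, baseline against one year in one arm of 12, by paired t test as a stand-in for the planned repeated-measures test. The standard error of the change is 6 × √2 / √12 = 2.45.

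| Common growth (units) | Growth / SE | Rejections with no device effect |
|---|---|---|
| 0 | 0 | 5% |
| 3 | 1.22 | 20% |
| 5 | 2.04 | 46% |
| 8 | 3.27 | 85% |

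**4. What age slope is plausible for cadence?** The documents give none. One illustrative model takes stature rising from 102 cm at age 4 to 150 cm at 12, cadence proportional to 1/√stature, and 120 steps/min at 126 cm. Cadence is then 120 × √(126/102) = 133 at age 4 and 120 × √(126/150) = 110 at age 12. That is 23 steps/min over 8 years, or about 2.9 per year. A range of 1 to 3 per year (in absolute size) is used below.

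**5. Chance imbalance in age.** For ages uniform on 4-12 the SD is 8/√12 = 2.31 years. The SE of the difference in mean age is 2.31 × √(2/12) = 0.94 years. A difference above 1 year occurs in 29% of allocations and above 2 years in 3%. At 1 to 3 steps/min per year, the SD of the resulting chance shift is 0.9 to 2.8 steps/min. The SE of the unadjusted cadence difference is 15 × √(2/12) = 6.1, and it already includes this shift if the age part lies within the SD of 15.

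**6. Precision from adjusting for age.** Residual SD = √(15² − (slope × 2.31)²), assuming the age part lies within the SD of 15.

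| Slope per year | Residual SD | t power, 12 per arm |
|---|---|---|
| none removed | 15.0 | 0.756 |
| 1 | 14.8 | 0.766 |
| 2 | 14.3 | 0.796 |
| 3 | 13.3 | 0.849 |

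These powers treat the slope as known. Estimating it costs one degree of freedom and inflates the variance of the arm difference by about 1 + 1/(22 − 2) = 1.05, so the SE by 1.025. The effective SDs become 14.8 × 1.025 = 15.2, 14.3 × 1.025 = 14.6 and 13.3 × 1.025 = 13.6. A check by 40,000 simulated trials per slope gave power of 0.75, 0.77 and 0.83. Age alone therefore pays at slopes of 2 to 3 and not at 1.

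**7. Three covariates together** (baseline, age, GMFCS level). Expected variance inflation is about 1 + 3/(22 − 3 − 1) = 1.17. The model breaks even once the three explain 1 − 1/1.17 = 14% of the variance. A baseline correlation of √0.14 = 0.38 would suffice on its own. Under the assumptions of step 2 that correlation is (144 + 48)/(144 + 48 + 36) = 0.84, where 48 is (3 × 2.31)².

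**8. GMFCS level.** If 12 of the 24 children were at each level (assumed) and allocation were unstratified, a split of 8/4 or worse would occur in 22% of trials.

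**The case against.** The strongest reply is that randomised, concurrent arms protect the treatment comparison. Step 2 confirms it. A reader might infer that growth biases the estimated device effect; it does not. Between arms the issue is efficiency, and the unadjusted standard error already counts the chance imbalance.

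Three other inferences also go beyond the text:

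- **Body size measured only at entry.** Procedures places one measurement before allocation and Equipment names no visit. A repeat is neither described nor excluded.
- **Allocation that ignores age and GMFCS level.** The Sample composition section describes sealed opaque envelopes and no method of sequence generation. Silence in a condensed article does not show an unstratified sequence.
- **All gait outcomes in raw body-size units.** Joint kinematics are not, the units of the kinetic data are not given, and cadence is named only in the sample-size basis.

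It is also fair to say that testing with and without the device at the same visit holds body size constant. However, Statistical analysis does not name that contrast. Scaling and covariates may be set out in a fuller plan, and the article nowhere claims that within-arm change alone proves efficacy. Finally, the slopes, growth amounts and error SD are assumptions.

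What survives is what the article fixes: separate within-arm tests over a year, and between-arm tests that take no covariate.

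**Conclusion.** The point holds in two parts. Change within an arm over 6 and 12 months cannot be read as a device effect, because growth alone can produce it: with an assumed measurement-error SD of 6, growth of 3 units gives a significant result in 20% of trials instead of 5%, and growth of 8 units in 85%. Between arms there is no systematic bias, but there is avoidable imprecision.

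The precision gain from age is modest and uncertain. It ranges from nothing at 1 step/min per year to about 7 percentage points of power at 3 per year (0.76 to 0.83, or 0.85 if the slope were known). This assumes ages uniform on 4-12 and an age part contained in the SD of 15. The baseline value may well contribute more, and part of the age effect would be absorbed by it, so the gains do not add. The change is worth making because it uses information collected before treatment.

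**What to change.** In the Statistical analysis section:

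1. Make the between-arm comparison the test of the device effect, using a linear model adjusted for the outcome's baseline value, age (or stature) and GMFCS level. The unadjusted ANOVA or Kruskal-Wallis result can stay as a sensitivity analysis.
2. State that within-arm change over 6 and 12 months is descriptive and not evidence of a device effect.

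Optional additions:

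- Repeat stature and mass at follow-up with the scale and stadiometer already listed, and report size-normalised walking values as a sensitivity analysis. Raw values stay primary.
- If the envelopes are not already stratified, block them by GMFCS level only. Adding age bands would make four strata averaging six children (24/4), and incomplete blocks could undo the balance sought.

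Cost: one degree of freedom per covariate (22 to 19 in all), the variance inflation in step 7, and a few minutes per visit if body size is repeated. Re-preparing envelopes is possible only for children not yet allocated.
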